#### PBI’s effect on health workers’ motivation

Drawing on mixed methods, this component will focus on health workers’ perceptions, satisfaction and motivation in relation to the implementation of the SSDI-PBI intervention. Specifically, we will assess whether and how changes in the working environment are perceived by health workers, and how these changes might have resulted in changes in motivation to provide high quality and quantity care. The qualitative approach will entail a series of IDIs with selected health workers from selected intervention health facilities, taking a retrospective approach of asking them to recall their perceptions of changes that have taken place in the implementation period, relating them to specific aspects of the intervention, and explaining pathways of change. We will conduct interviews only in intervention facilities with an aim of interviewing at least two providers per facility. We will also collect quantitative survey data that will assess perceptions of change in the working environment in both control and intervention facilities.

### The process evaluation component

Drawing on qualitative methods, the process evaluation will focus on fidelity of implementation (FOI), and consider adherence (defined in terms of content, schedule, and coverage) to the original intervention model and the contextual factors that mediated and affected adherence [34, 35]. This analysis will explore to what extent *in itinere* modifications - inevitable when concerned stakeholders are responding to and implementing a given intervention - hinder or enhance the effectiveness of the intervention itself. The process evaluation component will allow us: to delineate to what extent the SSDI-PBI intervention was delivered as initially planned and to explore heterogeneity in implementation processes across districts and facilities; to understand how the various stakeholders responded to the intervention and acted to modify, for better or for worse, its content; to identify contextual elements that affected the implementation of the SSDI-PBI intervention and to what extent these elements can explain heterogeneity in outcomes across districts and facilities.

Within this component we will pay particular attention to the implementation processes related to: the verification and counter-verification system, to understand its suitability and effectiveness within the framework of the SSDI-PBI intervention; the facility management structures and the interaction with the SSDI team in charge of the facility business plans, to understand the process of receiving and re-investing the performance rewards and the potential for “gaming” induced by these structures; and the role that district management teams play in relation to supervision, human resource allocation, and distribution of equipment and commodities, to identify potential changes in behavior in favor of incentivized facilities and services.

This portion of the study will rely on qualitative methods, conducted using a prospective approach. In line with standard practice in process evaluation [36] and with our own work in similar settings [37, 38], we will begin our work by convening a workshop with the SSDI-PBI core design and implementation team to develop a shared Theory of Intervention (TOI) and to identify the core 20–25 activities which fit this TOI, and are key to the intervention success from a theoretical point of view. Qualitative data will be collected to examine contextual factors that mediated the implementation and as such affected fidelity, and to explore how the various stakeholders responded to the intervention through adaptation and adoption. By “stakeholders” we are referring to anyone involved in the design and implementation of the intervention (i.e. the funding agency and its implementing partners, Ministry of Health (MoH) directorates, district management teams, PBI desk officers, as well as at least one health worker from each concerned facility). Sampling will be done via the snowball method wherein the study team will first be introduced by the funding agency and key programmatic personnel to those engaged in the SSDI-PBI program. This will assist the research team in identifying initial respondents. These respondents will be asked to assist in the identification of other respondents, who could facilitate an understanding of the themes and issues raised in the interview or related to the program generally.

### The costing component

The main objective of this component is to evaluate costs of the SSDI-PBI scheme to provide insights on the value for money associated with the intervention. The costs associated with PBI include the following cost categories: a.) start-up costs (design of program, training, initial dissemination); b.) ongoing management (including verification and counter-verification); c.) the cost of incentives themselves. These costs are incurred at the level of the Ministry of Health, its development partners (USAID), and the implementing agency (SSDI). The cost analysis will allow estimating the incidence of different cost categories, accruing the total costs of PBI. More specifically, we will be able to compare the total costs of start-up, implementation and management of the PBI scheme to the costs of financial incentives. For the majority of cost components, costs will be evaluated using the micro-costing approach, which requires that for each cost category, quantity of resources is identified and then multiplied by its unit costs. To do this we will rely heavily on support from the implementation team, asking to access their financial and cost management data. We will also request lists of participants who were engaged in key implementation activities (and approximate salary ranges across cadres of employment) in order to account for an allocation of staff time toward PBI activities in the event that time investment was not paid for.

### Overarching analysis & data protection

The ultimate aim of this research is to assess the effect that the SSDI-PBI intervention produces on the quantity and quality of care in light of the intervention implementation processes and at what cost. While the work is divided into components to ease data collection and analysis, the ultimate aim of this study is to triangulate and integrate information across components and data sources in order to address the overall study objective, and to provide a more nuanced interpretive analysis. Lead researchers across study components will convene to discuss and share findings upon completion of analysis of a given component.

### Quantitative data analysis

Quantitative data will be analyzed using Stata. Our analytical approach will largely rely on a controlled time-series analysis, building on data from 17 intervention and 17 control facilities. As such, the actual sample size will be 34. For each of the quantitative outcome indicators, we will include monthly data from the HMIS for the period Sept 2013 to Dec 2015 (or 12–24 months prior to and 12–15 months following PBI start). This will generate a total of 28 observation points for each of the 34 facilities included in the study. For each service provision indicator, we will compare developments over time across intervention and control facilities. Given that we could not assess actual data availability and completeness prior to data collection, we will do ex-post power calculations. We will assess the impact of the intervention on targeted service provision indicators using an interrupted time-series model with independent controls. In addition, given the availability of two single time points, we will rely on difference in differences modeling to assess changes in quality of care, using for example changes in staff numbers and qualification, availability of equipment and supply as proxies. This analytical component will draw upon primary data that will be collected in intervention and control facilities, as well as SPA data collected in January 2014, which will serve as a pseudo-baseline.

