The SSDI-PBI program aims to increase access, utilization, and quality of EHP services by linking rewards to service utilization and quality indicators across a range of conditions and services. Utilization, or quantity, indicators focus on increasing total counts in terms of services across the maternal health continuum of care (during antenatal, delivery and postpartum periods), newborn and child health, and HIV and AIDS care and treatment (see Table 1 for a list of quantity indicators). Quality indicators emphasize improvements in the broader facility environment and in the nature of how care is provided across 13 service areas (see Table 2 for a list of quality dimensions). Quality assessments are complemented by a community component wherein a series of focus groups (a component of “community scorecards”) and exit interviews are conducted with clients to gauge satisfaction. SSDI-PBI rewards are comprised primarily of quantity and quality scores, with community scores serving as a source of potential bonus payments. Rewards are paid to facilities upon achievement of set targets, but the rewards can only be used toward facility improvements and cannot be partially redistributed in the form of performance bonuses to individual health workers, which is common under other performance-based schemes. Another defining characteristic of the rewarding system is that procurement at the facility level is managed through existing SSDI finance and procurement structures rather than through facility-based personnel. Rewarded funds are invested in previously determined service improvement activities or strategies outlined in annual business plans, which are developed by facility staff in collaboration with SSDI staff. These plans outline the activities, procurements or technical support that facility staff intend to prioritize as a means to improve care.

**Table 1 Tab1:** Quantity Indicators used in SSDI-PBI

1.	Number of pregnant women starting antenatal care during the first trimester
2.	Number of women completing the four antenatal care visits
3.	Number of pregnant women receiving at least two doses of intermittent preventive therapy
4.	Number of births attended by skilled birth attendants (doctor, nurse or midwife)
5.	Number of 1-year-old children fully immunized
6.	Number of HIV-positive pregnant women who were initiated on antiretroviral therapy
7.	Number of HIV/AIDS cases screened for Tuberculosis
8.	Number of children receiving Vitamin A supplementation

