9.	Number of clients counseled for family planning
10.	Number of couples tested for HIV during HIV testing and counseling services
11.	Number of infants born by HIV positive mothers tested for HIV
12.	Number of women who receive postnatal care after delivery by skilled health workers within seven days
13.	Number of pregnant women attending antenatal care receiving iron supplementation

**Table 2 Tab2:** Quality Dimensions assessed in SSDI-PBI

1. General activities	
2. Follow-up assessment and HMIS	
3. Hygiene, environment, and sterilization	
4. Outpatient and inpatient consultation	
5. Maternity ward	
6. Antenatal consultation	
7. Family planning	
8. Vaccination and monitoring of newborns	
9. HIV/AIDS control	
10. Tuberculosis	
11. Laboratory	
12. Minor surgery	
13. Drug and commodity management	

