In terms of contending with the aforementioned limitations, our evaluation team seeks to be nimble and resourceful. We are drawing from multiple methods within both quantitative and qualitative approaches. Quantitatively, we collect primary data related to infrastructure and equipment, staff numbers and trainings, as well as health worker perceptions. Qualitatively, we directly collect IDI and FGD data across a broad range of respondents at facility, community and policymaker levels thereby inhibiting the domination of one single respondent type. We are also undertaking triangulation to identify points of convergence and divergence in the data. This study draws upon a substantial amount of secondary data. The utilization of secondary data, while imperfect, can present a means to capitalize on existing data thereby reducing costs while contending with time constraints. Furthermore, secondary data presents a means to overcome the absence of an evaluator-initiated baseline survey, to capture trends over time (in the case of HMIS data, specifically), and to fulfill a tenet of meaningful implementation research [41]. While having a short turnaround period poses limitations in terms of research, we also view it as an opportunity to generate knowledge and to inform implementation partners in a timely fashion—even as decisions are being made regarding how to expand an intervention.

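### Service-quantity effects rest on facility HMIS counts in a programme that rewards the same kind of counts and scores HMIS practice, so a recording shift at PBI start cannot be separated from a change in services

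*Protocol article*

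**What the plan says.** **Outcome source and model.** The Quantitative data analysis section fixes the source of the service-quantity outcomes: "For each of the quantitative outcome indicators, we will include monthly data from the HMIS", from September 2013 to December 2015. The effect on targeted indicators is to come from an interrupted time-series model with independent controls, using 28 monthly points in each of 34 facilities. The same section says that data availability and completeness could not be assessed before collection.

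**What the programme rewards.** The Study setting section describes the scheme as "linking rewards to service utilization and quality indicators across a range of conditions and services", and adds: "Utilization, or quantity, indicators focus on increasing total counts in terms of services across the maternal health continuum of care". Table 1 lists 13 such counts. On payment it says: "Rewards are paid to facilities upon achievement of set targets". Table 2 lists 13 scored quality dimensions, of which the second is "Follow-up assessment and HMIS".

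**Controls.** The section on service provision and health worker behavior matches controls on facility type, zone or district, distance to a main road and PQI status. Their stated purpose is to limit time-dependent bias.

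**Related features.** The process evaluation studies the programme's verification and counter-verification system, and the scope for gaming, by qualitative methods. The first research question compares incentivized with non-incentivized services. The Discussion rules out household surveys and direct observation for reasons of time and money.

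**The concern.** The recording system that supplies the outcome is one that the intervention acts on. From PBI start, an intervention facility has reason to record more fully the services that count towards its reward, and its HMIS practice is scored. A control facility has neither stimulus from PBI. A recording change of this kind would start at the interruption and in one arm, which is exactly the pattern that the model reads as an effect.

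Matching on facility type, location, road access and PQI status does not address this, and neither does a control series: it removes shared time trends, not a measurement change confined to the other arm. The article describes no comparison of HMIS counts with another source in both arms. The limitations name non-random selection, small sample and the lack of a primary baseline, but not incentive-driven recording.

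The results are meant to inform scale-up of PBI in Malawi, and costs are to be set against outcomes. A recording artefact could therefore be reported as added services. Should service counts serve as the outcome in the cost comparison, the error would carry into it; the costing section itself defines no cost-per-service figure.

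**Working it through.** **1. The plan's own figures.** September to December 2013 is 4 months, and 2014 and 2015 add 12 each: 4 + 12 + 12 = 28. Facilities: 17 + 17 = 34. Facility-months per indicator: 28 × 34 = 952. The stated figures reproduce. With 12 to 15 months after PBI start, 16 to 13 months remain before it.

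**2. Model.** Let S be services delivered and c the ratio of recorded to delivered services, so the recorded count is Y = c × S. Suppose S follows the same trend in both arms with no PBI effect, c moves from c0 to c1 at PBI start in intervention facilities, and c stays at c0 in controls. On the log scale:

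- change in level, intervention arm: log(c1) − log(c0)
- change in level, control arm: 0
- estimated effect on level: log(c1/c0), a rate ratio of c1/c0

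**3. Check by fitting.** A noise-free controlled interrupted time series was fitted to log counts over 28 months, 15 of them after the start, with a common trend and a true effect of zero.

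| Recording change | Level rate ratio | Slope rate ratio |
|---|---|---|
| 0.80 to 0.90, intervention arm only | 1.125 | 1.00 |
| 0.80 to 0.90, both arms | 1.00 | 1.00 |
| 1.10 to 1.00, intervention arm only | 0.909 | 1.00 |

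A one-arm change passes in full into the level estimate. The controls remove it only when it happens equally in both arms.

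**4. Size.** The document gives no completeness figures, so every c below is an assumption.

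| c0 | c1 | Spurious rate ratio c1/c0 |
|---|---|---|
| 0.95 | 1.00 | 1.05 |
| 0.90 | 0.95 | 1.06 |
| 0.85 | 0.95 | 1.12 |
| 0.80 | 0.95 | 1.19 |
| 0.70 | 0.90 | 1.29 |
| 1.05 | 1.00 | 0.95 |
| 1.10 | 1.00 | 0.91 |

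The last two rows are cases where counts were too high before PBI and verification brings them down. The assumed range runs from 0.91 to 1.29, so arithmetic alone does not fix the direction.

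**5. What c covers.** It combines two things: whether a facility-month-indicator cell is reported at all, and whether a reported cell is accurate. Unreported cells bias the counts in this way if they enter as zero; the article does not say how they are handled, which is ordinary analysis-plan detail and not criticised here. Under- or over-recording within reported cells biases the counts however missing cells are treated.

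**The case against.** The other side has several good arguments.

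- **Nothing shows that recording changed.** This stands. The document reports no recording shift in either arm, so the point concerns a risk.
- **The payment source is not named.** This stands. A reader might infer that rewards are computed from the very HMIS entries used as outcomes. The document shows overlap between the rewarded indicators and the outcome indicators, and says that rewards follow targets, but does not say which records are used for payment.
- **Verification exists.** It could restrain over-reporting or lower counts, so the tempting reading that every count is biased upward does not follow. Verification does not remove the problem, however. It is listed among the costs of running PBI, nothing describes it in control facilities, and its effectiveness is an open question for the process evaluation. A correction made in one arm is itself a recording change.
- **The motive is weak.** Rewards cannot reach individual workers and procurement is run by SSDI. This makes deliberate inflation less likely, but fuller recording needs no personal gain, and HMIS practice is scored in any case.
- **Incentivized and non-incentivized services are compared.** This is a real partial check, since payment-driven recording should concentrate in the rewarded counts. It cannot detect a general improvement in HMIS practice, which would raise both, and a gain confined to rewarded counts would also fit a true incentive effect.
- **The authors concede imperfect data.** They do: "The utilization of secondary data, while imperfect, can present a means to capitalize on existing data". That caveat is generic and does not mention a change in recording caused by the incentive.

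**Conclusion.** The point holds as a risk of differential measurement that the planned model cannot detect or remove. The outcome counts come from facility HMIS, the programme rewards counts of the same kind, and it scores HMIS practice in intervention facilities. A one-arm recording shift at PBI start would appear one for one in the effect estimate, as c1/c0. The most likely direction is upward for incentivized counts, for example 1.12 for a move from 0.85 to 0.95; verification could turn it downward, for example 0.91 for a move from 1.10 to 1.00. These sizes rest wholly on assumed recording ratios and on unchanged recording in controls.

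The document does not support the stronger claims that recording did change, that all counts are inflated, or that HMIS entries are the basis of payment. Nor does the point reach the difference-in-differences analysis of quality, which uses primary facility data and the SPA pseudo-baseline.

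**What to change.** 1. **Model completeness as an outcome.** Fit the same controlled time-series model to HMIS reporting status (reported or not, per facility, month and indicator) in all 34 facilities. Repeat the count analysis on reported cells only. This uses data already being extracted. It tests missing reports; it does not test accuracy within reported cells.
2. **Use the planned contrast.** Present incentivized against non-incentivized indicators as a partial check for payment-driven recording, and state that it does not catch a general improvement in HMIS practice.
3. **Limit the conclusion.** Describe the result as a change in recorded services unless these checks show no differential recording shift. Name incentive-driven recording as a limitation in either case.
4. **Optional.** Compare registers with HMIS for a few indicators at the facility visits already planned in both arms, and report it descriptively. It should not become a correction factor or a condition for the conclusion: two or three indicators in two months are too few to correct 13 indicators over 28 months, and registers filled in by the same staff cannot reveal altered registers.

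The cost is a little more analysis and a more cautious headline claim; the optional step lengthens the visits slightly.

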### Qualitative data analysis

All qualitative interviews will be tape-recorded, transcribed and translated into English. Qualitative data will be analyzed using a hybrid approach. We will first identify themes from a selection of rich and nuanced transcripts – an inductive approach [39]. We will later apply this template of codes to the remaining transcripts through a deductive approach [40]. We will adopt in-vivo coding (using NVivo 10), with codes, categories, and themes emerging as we proceed through the data, although the initial coding process will be guided by the research questions. We will apply data triangulation as we will compare information across data sources to capture multiple perspectives of the same research question, and analyst triangulation as at least two researchers will code and interpret each set of data.

## Discussion

PBI programs are complex and questions remain in terms of the potential for such programs to improve the quality of care and spark reductions in morbidity and mortality. The aim of SSDI-PBI in Malawi is to increase service utilization and stimulate better quality of care by linking payments to strategies aimed at improving providers’ working environments and in doing so, empowering providers with the means to provide care of an adequate standard.

The overarching purpose of this study is to contribute robust evidence to a growing body of literature examining the process, impact and cost-effectiveness of PBI programs in SSA. We also aim to generate knowledge regarding how programs such as SSDI-PBI are woven into the health system, how they are perceived by patients and providers alike, and to what extent they are cost-effective. We view this research as particularly useful because it examines a non-conventional PBI model, which does not entail monetary incentives or financial autonomy at the facility level. Such a model has not been studied in the literature.

This study design was conceptualized with a relatively small budget and a relatively short study period (approximately one year) to rapidly meet the need of informing the implementation of the intervention. Given the broad scope of the PBI intervention in respect to the range of services being incentivized, time and funding constraints do not allow for a detailed assessment of cost, nor is it feasible to undertake time or labor intensive endeavors such as community-based household surveys to assess health-seeking behavior, or direct observations to assess quality of care processes. In respect to producing robust effect measures, the main limitation of this study design is that it had to be adapted to a non-randomized intervention. Given that study districts and intervention facilities were chosen by the MoH based on political and logistical considerations rather than a random selection of health facilities and districts, selection bias was introduced. Furthermore, our study sample is limited to the relatively small scope of the intervention (17 health facilities), potentially resulting in low statistical power. As a consequence, we might not be able to demonstrate statistical significance of observed impacts. Finally, the fact that the start of the PBI program is not aligned with the external evaluation research further restricted the design, as baseline information on the performance of essential health service provision could not be based on primary data collection on sets of indicators directly linked to specific outcome measures. As a result, different quasi- and non-experimental study approaches and a heavy reliance on secondary data sources was required to address potential threats to validity.

In terms of contending with the aforementioned limitations, our evaluation team seeks to be nimble and resourceful. We are drawing from multiple methods within both quantitative and qualitative approaches. Quantitatively, we collect primary data related to infrastructure and equipment, staff numbers and trainings, as well as health worker perceptions. Qualitatively, we directly collect IDI and FGD data across a broad range of respondents at facility, community and policymaker levels thereby inhibiting the domination of one single respondent type. We are also undertaking triangulation to identify points of convergence and divergence in the data. This study draws upon a substantial amount of secondary data. The utilization of secondary data, while imperfect, can present a means to capitalize on existing data thereby reducing costs while contending with time constraints. Furthermore, secondary data presents a means to overcome the absence of an evaluator-initiated baseline survey, to capture trends over time (in the case of HMIS data, specifically), and to fulfill a tenet of meaningful implementation research [41]. While having a short turnaround period poses limitations in terms of research, we also view it as an opportunity to generate knowledge and to inform implementation partners in a timely fashion—even as decisions are being made regarding how to expand an intervention.

This study also seeks to draw upon a theory as a means to inform the nature of the research and to guide the research team in terms of sampling and data analysis. We view the development of theory as an essential though under-emphasized concept within PBI literature. This evaluation places an emphasis on the health facility (inclusive of the staff, infrastructure and equipment therein), which the study team and implementing team have determined represents a meaningful starting point for an examination of PBI (given the manner in which the program compels tremendous shifts in terms of how, when, how often and at what cost providers are capable and expected to provide care). Furthermore, the actions of providers and the nature and quality of their engagement with patients are critical factors in determining whether and to what degree morbidity and mortality are ultimately reduced. While our theory emphasizes the effect of PBI within the health facility, we see several points of entry to inform future consideration of the theoretical underpinnings of PBI. For example, PBI lays the foundation for national level policies and priorities that ultimately redirect practices at zonal, regional, district and community levels. On an interpersonal level, PBI affects how patients and providers interact with and perceive one another (and possibly how the parties perceive the health system more generally). Given the web of entry points wherein one could consider theoretical underpinnings of PBI, it is challenging to focus on a particular sphere or set of indicators, but we view an expansion of theory-driven research as necessary in guiding future research in this field.

Our study design contributes to the evaluation literature by providing an example of how sound implementation research can be done despite time and budget constraints as well as constraints due to the size of the intervention. We view this contribution as crucial particularly as PBI programs continue to expand and ministries of health and finance -- as well as funders and program implementers -- are faced with decisions regarding whether or how programs should be adapted or expanded and at what cost. We view a more well-rounded examination as a powerful tool in not only guiding programmatic and policymaker decisions, but also as a means to guide fellow researchers as they consider how to evaluate health programs in a comprehensive, affordable, meaningful and timely manner.

